## Abstract

**Background::**

Although many mothers initiate breastfeeding, supplementation with human-milk substitutes (formula) during the birth hospitalization is common and has been associated with early breastfeeding cessation. Colostrum hand expressed in the last few weeks before birth, known as antenatal colostrum expression (ACE), can be used instead of human-milk substitutes. However, evidence is lacking on the efficacy of ACE on breastfeeding outcomes and in non-diabetic mothers.

**Methods and Planned Analysis::**

This multicenter stepped-wedge cluster (nested) randomized controlled trial aims to recruit 945 nulliparous pregnant individuals. The trial is conducted in two phases. During Phase 1, control group participants are under standard care. During Phase 2, participants are randomized to ACE instruction via a pre-recorded online video or a one-on-one session with a midwife. Adjusted logistic regression analysis will be used to examine the relationship between ACE instruction and breastfeeding outcomes.

**Research Aims and Questions::**

Primary aim: (1) Does advising pregnant individuals to practice ACE and providing instruction improve exclusive breastfeeding rates at 4 months postpartum? Secondary research questions: (2) Do individuals who practice ACE have higher rates of exclusive breastfeeding during the initial hospital stay after birth? (3) Is teaching ACE via an online video non-inferior to one-on-one instruction from a midwife? (4) Does expressing colostrum in pregnancy influence time to secretory activation, or (5) result in any differences in the composition of postnatal colostrum?

**Discussion::**

Trial findings have important implications for maternity practice, with the online video providing an easily accessible opportunity for ACE education as part of standard antenatal care.

Key MessagesEvidence is lacking on the effectiveness of antenatal colostrum expression on breastfeeding outcomes and in non-diabetic mothers.This stepped-wedge cluster (nested) randomized controlled trial is being conducted at multiple hospital sites in Western Australia and recruits first-time mothers.To our knowledge, this is the first large scale study being conducted in the non-diabetic population of pregnant individuals that will determine the effectiveness of various formats of antenatal colostrum expression education on breastfeeding outcomes.

## Background

Exclusive breastfeeding is when the infant receives only human milk, except for oral medicines, vitamins, and minerals, and it is recommended for the first 6 months of life (World Health Organization [WHO] & the United Nations Children’s Fund [UNICEF], 2021). Supplementation with human milk substitutes (like commercial infant formula) during the initial hospital stay after birth is common in Australia, with approximately one-third of infants receiving human milk substitutes during the birth hospitalization (Netting et al., 2022). Supplementation with human milk substitutes jeopardizes exclusive breastfeeding practices and increases the risk of early breastfeeding cessation (McCoy & Heggie, 2020; Vehling et al., 2018). As an alternative to the use of human milk substitutes, colostrum can be expressed in pregnancy, stored in a freezer, and taken to the hospital at the time of birth. Colostrum expressed in pregnancy can be defrosted and fed to infants during the initial hospital stay if additional supplementation is required. Supplementation with a parent’s own colostrum instead of human milk supplements may protect exclusive breastfeeding practices in hospitals.

Historically, there have been concerns that antenatal colostrum expression (ACE) can affect hormones that promote the onset of labor (e.g., oxytocin). To date, there has been only one large-scale and high-quality randomized controlled trial (RCT) of ACE conducted among pregnant individuals with low-risk diabetes (the Diabetes and Antenatal Milk Expressing [DAME] study). The DAME trial demonstrated that ACE twice per day for up to 10 min beginning at 36 weeks gestation was safe for pregnant individuals with diabetes who were otherwise at low risk of pregnancy or general health complications. In the DAME trial, there was no difference observed between randomization groups for admissions to the Neonatal Intensive Care Unit (NICU) or mean gestational age at birth (Forster et al., 2017).

A scoping review by Foudil-Bey et al. (2021) evaluated ACE outcomes and concluded that there was an increasing interest in the safety, efficacy, and acceptability of ACE. Specific to this protocol, Foudil-Bey et al. (2021) found that of the 20 studies included, breastfeeding success was not clearly defined, and the duration of follow-up varied greatly between studies. Similarly, the implementation of ACE across maternity hospitals or other prenatal care settings is unclear. Across the United Kingdom, the National Health Service (NHS) guidelines at major maternity centers advise that any pregnant individual can practice ACE from 36 weeks gestation onward, but it is promoted as being particularly useful for mothers at risk of low milk supply or if the infant has an increased risk of being born with hypoglycemia. The NHS states that other individuals who may benefit from ACE are those planning an elective Caesarean birth or with a body mass index (BMI) > 35 kg/m^2^. Some health districts across Australia and New Zealand encourage ACE for pregnant individuals with medical conditions that might cause the infant to have hypoglycemia at birth, or potentially if the mother has had previous breastfeeding difficulties. Information brochures are accessible online detailing how to hand express and store colostrum in pregnancy and describe situations where ACE may be beneficial (i.e., gestational diabetes mellitus). Currently, ACE is not routinely or universally promoted for all eligible pregnant individuals entering maternal health care. This is likely due to a paucity of evidence regarding the efficacy of ACE in improving breastfeeding rates in the general pregnant population and a lack of safety data for ACE in non-diabetic populations that may otherwise be considered to have a high-risk pregnancy. Further, little research has been carried out on the optimal delivery methods for information and instruction related to ACE.

Some qualitative research suggests ACE may shorten the time until a mother experiences onset of copious human milk (secretory activation, previously known as Lactogenesis II; Demirci et al., 2019); however, there is currently no high-quality evidence to support this claim. ACE has the potential to improve breastfeeding outcomes for all pregnant individuals, not just those with health conditions such as diabetes, or with previous breastfeeding difficulties. Results of this trial will inform standard antenatal care processes for the general population of pregnant individuals. In addition, the analysis of any effect(s) that ACE may have on postnatal colostrum composition is important, given the vast health benefits of colostrum for infants.

The trial has been designed to answer the following research questions:

(Primary aim) Does advising pregnant individuals to practice ACE and providing instruction improve exclusive breastfeeding rates at 4 months postpartum, compared to standard care? The hypothesis is that pregnant individuals who receive ACE education will have higher rates of exclusive breastfeeding at 4 months (EBF4M) compared to pregnant individuals in the control group receiving standard care.Do pregnant individuals who receive ACE instruction have lower rates of humanmilk substitute (formula) use during the initial hospital stay after birth compared to mothers who do not receive ACE instruction? The hypothesis is that mothers who receive ACE instruction will have lower rates of humanmilk substitute use during the initial hospital stay.Is teaching ACE via an online video non-inferior to one-on-one instruction from a midwife [in terms of breastfeeding outcomes]? The hypothesis is that teaching ACE via an online video is non-inferior to one-on-one instruction from a midwife.Does expressing colostrum in pregnancy influence time to secretory activation, compared to not expressing colostrum in pregnancy? The hypothesis is there will be no difference in the time it takes until secretory activation occurs between individuals who practice ACE and individuals who do not practice ACE.Does expressing colostrum in pregnancy result in any differences in the composition of postnatal colostrum? The hypothesis is that there will be no differences in post-birth colostrum content in macronutrients and key bioactive compounds—Immunoglobulin A (IgA), Transforming Growth Factor (TGF)-beta 1, soluble CD14, Lactoferrin and Epidermal Growth Factor (EGF)—between individuals who express colostrum antenatally, compared to individuals who do not.

## Methods

### Research Design

The ACE Study is a stepped-wedge cluster (nested) randomized controlled, investigator-blinded, multicenter, non-inferiority trial with parallel intervention groups. The rationale for this trial design (Phase 1, a period where the control group data will be collected, and Phase 2, randomization of participants to either the midwife [MW] or video instruction [VI] groups) was chosen as it provides a quarantined period of observation and data collection from the control group. Randomizing participants to all three groups simultaneously was not performed as this would risk contamination (via artificially increasing knowledge above standard care) in the control group and hospital staff delivering care. Pregnant individuals attending the same antenatal classes may discuss and share aspects of their care, and hospital staff may inadvertently promote ACE to the control group. Each hospital (site) is a cluster, with the Phase 1 start time being dependent on hospital logistics (for example ability to carry out staff training, ethics, and governance approvals). During Phase 2, nested within each cluster, individual participants are randomized (50:50) to one of two invention arms. The trial has a primary endpoint of 4 months postpartum, specifically the rate of EBF4M. All enrolled participants will have data collected until 4 months postpartum. The endpoint in this trial was chosen as a timepoint where the achievement of the proposed level of breastfeeding would be significant, given previous national indicators (Australian Bureau of Statistics, 2017–2018).

#### Choice of comparators

Participants in the non-intervention (control) group will receive standard maternity care. Participants individually randomized to one of two intervention arms will receive the same ACE instruction from either a one-on-one session with a midwife (MW group) or ACE instruction from an online video (VI group). Participants in the MW group have a 15 to 20-minute one-on-one consultation with a midwife (also trained as an International Board-Certified Lactation Consultant [IBCLC]) who provides information and instruction on how to hand express, collect, and store colostrum in pregnancy. The midwives providing the ACE instruction are trained in the study protocol for teaching hand expression in pregnancy. Participants randomized to this group can ask questions and practice the technique directly with the midwife. Participants randomized to the VI group receive a link to an online 16-minute video they can watch at home as many times as they like. The ACE video used in this trial was developed by members of the ACE Study research team to determine whether an online instructional video could improve pregnant individuals’ knowledge and confidence around breastfeeding. The video was made specifically for pregnant individuals and provides education and instruction on how to hand-express, collect and store colostrum during pregnancy. In a previous evaluation of the video, 95 pregnant individuals completed questionnaires before watching the video, and again afterwards; researchers found the video improved knowledge scores and self-reported confidence around ACE (O’Sullivan et al., 2019).

#### Ethics

This trial is being conducted according to the strict protocols of the National Health and Medical Research Council (NHMRC) National Statement on Ethical Conduct in Human Research (NHMRC et al., 2007). All procedures involving human participants/patients were approved by the Human Research Ethics Committee (HREC) at Edith Cowan University (ECU) on July 8, 2019; the HREC approval number is 2019-00572-[name]. The ACE Study has been approved by Ramsay Health Care Western Australia and South Australia, HREC (reference number: 1901), and Women and Newborn Health Service Ethics Committee (RGS0000001504). The ACE Study has been registered as a clinical trial with the Australian New Zealand Clinical Trials Registry (Universal Trial Number: U1111-1232-1397, https://anzctr.org.au/Trial/Registration/TrialReview.aspx?id=377448).

#### Study framework

The ACE Study draws on the pragmatist paradigm and uses a mixed methods model with an embedded experimental design to collect quantitative and qualitative data (Creswell, 2014). A philosophical movement that originated in the 1870s, pragmatism originated when a group of scholars rejected traditional ideas and assumptions about the nature of reality, knowledge, and inquiry (Kaushik & Walsh, 2019). Pragmatism is based on the assumption that researchers use philosophical and methodological approaches that are best suited to their research problem (Kaushik & Walsh, 2019). One of the major underpinnings of a pragmatist paradigm is that a person’s perceptions of the world, or their knowledge, are influenced by their social experiences (Kaushik & Walsh, 2019). In the ACE study, quantitative data collection is given priority and guides the study while the qualitative method of data collection is nested within the larger study design (Alavi et al., 2018; Figure 1). Quantitative and qualitative data from the ACE study will be analyzed separately; however, the findings from the qualitative data will be used to understand the participants’ views within the context of the experimental intervention (Creswell, 2014).

**Figure 1. fig1-08903344231215074:**
[figure not shown]
Theoretical Framework for the ACE Study. *Note*. ACE = antenatal colostrum expression.

### Setting and Relevant Content

Western Australia (WA) accounts for 33% of the Australian continent and 10% of the country’s population. Perth is the capital city and home to 75% of the state’s population. It stretches along the western coastal border to the north and south of the city. Proposed recruitment sites include Joondalup Health Campus Hospital (JHC), WA; Perth Pregnancy Centre, WA; Armadale Hospital, WA; Glengarry Private Hospital, WA; Fiona Stanley Hospital (FSH), WA; Bunbury Hospital, WA; and Busselton Hospital, WA. JHC is the largest healthcare facility in the northern suburbs of Perth. JHC is a metropolitan, private, and public hospital in a higher socioeconomic area. The Australian Bureau of Statistics (2016) Socio-Economic Indexes for Areas (SEIFA) ranks areas relative to socioeconomic advantage and disadvantage, using decile ranking (1–10). Decile 1 represents low socioeconomic communities with greater disadvantage and 10 represents greater socioeconomic advantage. JHC is located in an area with a decile score of 7. JHC includes participants recruited through the ORIGINS cohort as the ACE Study is a sub-project of The ORIGINS Project. JHC has approximately 4057 births per year, with a 39% Caesarean section rate (Hutchinson et al., 2019). Pregnant individuals receiving antenatal services at Perth Pregnancy Centre most commonly birth at JHC. Armadale Hospital is a metropolitan public hospital in a low socioeconomic area (decile score 1) with approximately 2513 births per year and a 23% Caesarean section rate (Hutchinson et al., 2019). Glengarry Private Hospital is in a high socioeconomic area (decile score 10) with approximately 593 births per year and a 49% Caesarean section rate (Hutchinson et al., 2019). FSH is a government hospital located in Murdoch, a high socioeconomic area (decile score 9), 15 km south of Perth’s central business district. FSH is the major tertiary hospital in the southern metropolitan area, with about 3600 births per year and a Caesarean section rate of 34% (Hutchinson et al., 2019). Bunbury (decile score 6) and Busselton (decile score 1) Hospitals are public hospitals in a regional area in Southwest, WA. There are approximately 1557 births per year in the South West Health Region and a 27% Caesarean section rate (Hutchinson et al., 2019).

#### Breastfeeding in Australia

In Australia, National Health Survey data shows that the prevalence of exclusive breastfeeding at 4 months of age is 61%, and drops to 29% by 6 months of age, with rates remaining consistent since 2014 to 2015 (Australian Bureau of Statistics, 2017–2018). The more recent National Health Survey data (2020 to 2021) was collected online during the COVID-19 pandemic and should be used for point-in-time analysis only and not be compared with previous survey data. The National Health Survey data for 2017 to 2018 came from a sample of approximately 21,300 people across Australia. Data was collected during personal interviews. One person was interviewed per household and provided breastfeeding data about one child in the household.

In Australia, those individuals not breastfeeding to 6 months are more likely to be primiparous, overweight or obese, have lower education, and smoke cigarettes (Moss et al., 2020). The primary reasons for not breastfeeding to 6 months in Australia include the perception of insufficient milk supply and other breastfeeding difficulties (e.g., latching issues, pain, expressing is too hard; Moss et al., 2020).

## Sample

The target population for this trial are nulliparous pregnant individuals aged 18 or older.

### Inclusion Criteria

Individuals are eligible if they have a singleton pregnancy, have adequate English language skills to provide informed consent, are willing to participate in the trial, are planning to give birth at one of the trial sites, and intend to breastfeed.

### Exclusion Criteria

The exclusion criteria are listed in Table 1. Individuals who develop any relevant maternal or infant medical conditions listed as exclusion criteria will not be eligible to participate/will be withdrawn from the trial.

**Table 1. table1-08903344231215074:** PICO (Population, Intervention, Comparison, Outcomes) for the ACE Study.

Study Component	Details
Population	Inclusion criteria
	● Nulliparous individuals
	● Singleton pregnancy
	● Able to read and speak in English
	● Planning to breastfeed
	● Willing to participate in the trial
	● Planning to give birth at one of the trial sites
	Exclusion criteria
	● EPDS score ≥13, or PASS score ≥26
	● Diabetes (pre-existing and pregnancy-induced)
	● Pre-eclampsia
	● Placenta previa
	● Antepartum hemorrhage
	● History of threatened/actual premature labor
	● Cervical incompetence
	● Fetal anomaly (cleft palate, down-syndrome, heart defect, neural tube defects)
	● Fetal compromise (polyhydramnios, known inter-uterine growth restriction)
	● Preterm birth (<37 weeks gestation)
Intervention	Intervention components in addition to standard maternity care during phase 2 include:
	● Oral and written information on antenatal colostrum expression: commence hand expressing from 37 weeks gestation, twice a day for 3-5 minutes per breast (maximum 10 minutes); and information on safe storage of colostrum during pregnancy
	● One-on-one ACE education session with midwife/IBCLC *or*
	● Unlimited access to an online 16-minute ACE instructional video
Comparison	Control group will receive standard maternity care
Outcomes	Primary outcome:
	● Exclusive breastfeeding at 4 months postpartum (EBF4M) [phase 1 control period versus phase 2 ACE groups (combined)]
	● Secondary outcomes:
	● Exclusive breastfeeding at 1, 4, 8, 12, and 16 weeks postpartum [MW intervention group versus the VI intervention group]
	● Exclusive breastfeeding from birth to discharge
	● Time to secretory activation
	● Colostrum composition after birth: macronutrients (lactose, protein, fat content), IgA, soluble CD14, Lactoferrin, EGF, and TGF
	Other outcomes:
	● Maternal attitudes to infant feeding
	● Breastfeeding self-efficacy
	● Time from starting ACE (obtained from milk-expressing diaries) until labor
	● Post-term induction rate
	● Gestational age at birth
	● Infant admission to special care nursery

In addition to our in-person recruitment methods, study posters are displayed at trial sites that contain an overview of the trial and ask pregnant individuals to complete an online expression of interest survey (EOI) if they are interested in participating. The study posters contain a quick response code that links to the EOI survey. The EOI containing a link to the PIF is provided for pregnant individuals to read before completing the EOI survey. After the EOI is completed, a researcher will contact the pregnant individual via telephone and provide the individual with an opportunity to ask questions before gaining verbal consent and sending out the electronic consent form. The flow of participants through the trial from recruitment to completion is shown in Figure 2.

**Figure 2. fig2-08903344231215074:**
[figure not shown]
The ACE Study Flowchart. *Note.* EBF = Exclusive breastfeeding; EBF4M = Exclusive breastfeeding a 4 months. *Phase 1 control participants complete a 4-month observation period before recruitment and randomization of intervention participants. **Intervention phase. ^1^Telephone-administered or completed online by participants who cannot complete via telephone.

### Sample Size

The research team has used a control group estimate for the primary outcome, EBF4M, of 27% based on the Australian National Infant Feeding Survey (Australian Institute of Health and Welfare, 2011). This represented the best available, nationally representative breastfeeding data at the time of study design.

The research team hypothesized that an EBF4M rate of 45% will be achieved in both intervention groups. An alpha of 0.05 has been selected for the sample size calculations as (1) the tests are one-sided and (2) there are two primary hypothesis tests to be carried out. An *n* of 271 per group will be required to have over 80% power to detect a difference between the MW and VI groups, independently, as well as the control group. This will demonstrate superiority by a margin of at least 5% based on a difference in proportions using the normal approximation with an intraclass correlation of 0.01. With this *n* (271) in both the MW and VI groups, and assuming a rate of 45% will be observed for EBF4M within both intervention groups, the trial will have 80% power to demonstrate non-inferiority with a lower equivalence rate of 32%; based on the difference in proportions using the normal approximation. This lower equivalence rate was deemed acceptable as it represents the same increase over the control group as the primary analysis (i.e., 5%). Data will be analyzed based on the principles of intention to treat and per-protocol analysis, with non-inferiority concluded if both analyses produce the same results (Angeli et al., 2020; Tripepi et al., 2020). A loss to follow-up rate of 15% is anticipated; therefore, the research team estimates that 315 pregnant individuals will be recruited into each group to achieve sufficient follow-up data for analysis. Rolling recruitment across multiple hospital sites will be required to achieve the recruitment target of 945 participants.

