## Outcomes/Measurement

Details of the primary and secondary outcome measures are provided in Table 4. In addition to recording data related to the primary and secondary outcomes, infant admission to the special care nursery (SCN), gestational age at birth, the post-term induction rate and time from starting ACE (obtained from expressing diaries) until going into labor will be recorded for MW and VI group participants to determine if ACE influences these additional outcomes.

**Table 4. table4-08903344231215074:** Details of the Outcome Measures Used in the ACE Study.

Outcome Measure	Measurement	Details of Measure
Primary outcome		
Exclusive breastfeeding at 4 months postpartum (EBF4M)	4-month postpartum questionnaire	Difference, between the control group and intervention groups combined (MW and VI), in the proportion of infants EBF4M
Secondary outcomes		
Exclusive breastfeeding during the initial hospital stay	Use of human milk substitutes in the hospital (medical records), 1- week postpartum questionnaire	Difference, between the control group and the intervention groups (MW and VI), in the proportion of infants exclusively breastfed in hospital
Exclusive breastfeeding at 1, 4, 8, 12 and 16 weeks postpartum	Postpartum questionnaires	Difference, between the two (MW and VI) groups, in the proportion of infants exclusively breastfed at 1, 4, 8, 12 and 16 weeks
Secretory activation (SA)	1- week postpartum questionnaire	Difference, between the control group and intervention groups (MW and VI), in the proportion of mothers who have SA at ≤ 1 day, 2-3 days, or >3 days
Colostrum composition after birth	Colostrum analysis: Macronutrients, EGF, IgA, soluble CD14, Lactoferrin and TGF	Difference, between the control group and intervention groups (MW and VI), in post-birth colostrum composition *(optional component for participants who opt-in only)*
Other outcomes		
Maternal attitudes to infant feeding	Iowa Infant Attitude Scale (IIFAS)	Difference, between the control group and intervention groups combined (MW and VI), scores on the IIFAS
Breastfeeding self-efficacy	Breastfeeding Self-Efficacy-Short-Form (BSES-SF)	Difference, between the control group and intervention groups combined (MW and VI), in BSES-SF scores
Post-term induction rate	Medical data	Difference, between the control group and intervention groups combined (MW and VI) in post-term induction rate

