## Planned Data Analysis

Data will be analyzed using SPSS (Version 29) or R. The primary outcome variable is EBF4M postpartum (yes or no). The secondary outcome variables are any or exclusive breastfeeding (at 1/4/8/12/16 weeks postpartum—analyzed separately), supplementation with a human milk substitute in the hospital (yes or no), time of secretory activation (≤ 1 day, 2–3 days, or > 3 days postpartum) which are all dichotomous. Other outcome variables are infant admission to SCN (yes or no; dichotomous) and gestational age at birth (continuous). Any or exclusive breastfeeding at 1, 4, 8, 12, and 16 weeks postpartum, use of human milk substitutes in hospital, infant admission to SCN (dichotomous outcomes), and time of secretory activation (nominal outcome) will be assessed (and reported) both using unadjusted analysis (a basic comparison of proportions) and using an adjusted analysis (mixed-effects logistic regression, adjusted for maternal age, socioeconomic status, mode of delivery and potentially other hypothesized confounders). Gestational age at birth (continuous outcome) will similarly be assessed (and reported) both using unadjusted analysis (Student’s *t* test) and adjusted analysis (mixed effects linear regression, if modeling assumptions are met adjusted for maternal age, socioeconomic status, and potentially other confounders). The mixed effects models will incorporate a site variable both as a fixed effect, addressing any inter-site differences, and as a random effect, accounting for any inherent within-site correlation in the data resulting from the clustered design. The decision to include variables as confounders for adjustments in the models is based on both hypothesized and established (from related literature) relationships with the outcomes and variables of interest. An analysis of variance (ANOVA) test will be used to compare two models, one within and one without a site, by intervention interaction variable. If the model with the interaction term is deemed to be a better fit, then only pre-specified subgroup analysis will occur, which is a per-site analysis using the same models as described above. Missing data will be reported (as count and percentage) by variable and group. If problematic, multiple imputation (by chained equations) will be used to impute missing values, with reported effect estimates then calculated by pooling across models run on imputed datasets. A level of significance of *p* < 0.05 will be used, and the research team will use confidence intervals to give context to outcome variability.

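### The non-inferiority rule asks that two analyses agree, not that both exclude the margin, and the margin protects against a no-benefit video only if the planning rates hold

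*Protocol article*

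**What the plan says.** Sample Size, in the protocol article, fixes both the limit and the rule.

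- Planning rates: a "control group estimate for the primary outcome, EBF4M, of 27"%, and, for the two instruction arms, "assuming a rate of 45% will be observed for EBF4M within both intervention groups".
- Limit: with 271 per arm, "the trial will have 80% power to demonstrate non-inferiority with a lower equivalence rate of 32"%, described as based on a difference in proportions.
- Reason for the limit: "it represents the same increase over the control group as the primary analysis (i.e., 5"%).
- Rule: after naming the intention-to-treat and per-protocol analyses, "with non-inferiority concluded if both analyses produce the same results".
- Error rate: alpha 0.05, with one-sided tests.

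The same section sizes MW and VI separately against control, for superiority by at least 5 points. Table 1 and Table 4 define the primary comparison with the two arms combined.

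Table 4 describes the MW-versus-VI outcome as "Difference, between the two (MW and VI) groups, in the proportion of infants exclusively breastfed at 1, 4, 8, 12 and 16 weeks". Planned Data Analysis states "A level of significance of *p* < 0.05 will be used" and gives confidence intervals the role of context for variability. It compares no confidence limit with a margin.

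**The concern.** A non-inferiority claim needs a confidence limit that excludes a stated margin. The written rule instead asks whether two analyses agree, and they can agree that non-inferiority was not shown. Nothing later in the article supplies the missing condition.

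The limit has its own weakness. As a rate of 32% it is tied to the assumed 45% and 27%. As a difference it is 13 points whatever the rates turn out to be. The two readings part as soon as MW is not at 45%, and the stated reason for the limit (5 points above control) holds under neither reading if control is not near 27%. Setting and Relevant Content, in its paragraph on breastfeeding in Australia, reports a national rate of 61% for exclusive breastfeeding at 4 months.

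At stake is the practical conclusion of the nested comparison: whether an online video can stand in for a one-on-one midwife session.

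**Working it through.** **Inputs (Sample Size unless noted).** Control 27%; MW and VI 45%; limit 32%; n = 271 per arm; one-sided alpha 0.05 (z = 1.645); intraclass correlation 0.01, stated with the superiority calculation. National rate 61% (Setting and Relevant Content). Assumed here: the number of sites, and the share of each arm that is per protocol.

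**Formula.** With margin M, SE = √[p_MW(1−p_MW)/n + p_VI(1−p_VI)/n], and the probability of passing is Φ((M − (p_MW − p_VI))/SE − 1.645).

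**1. The protocol's own 80%.** M = 45 − 32 = 13 points. SE = √(2 × 0.45 × 0.55/271) = 0.0427. Power = Φ(0.13/0.0427 − 1.645) = 92% without clustering. With design effect 1 + (271/k − 1) × 0.01 for k = 5, 6 or 7 sites, the design effect is 1.53, 1.44 or 1.38 and power is 79%, 81% or 83%. The stated 80% is therefore reproduced within 2 points for five or six sites. The calculation behind it is a test against a 13-point margin.

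**2. What the margin gives up.** Assumed benefit 45 − 27 = 18 points. Given up 13/18 = 72%; kept 5 points (28%).

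**3. Base case for a no-benefit video.** MW 45%, VI 27%: SE = 0.0405, and Φ((0.13 − 0.18)/0.0405 − 1.645) = 0.2%. A video at 32% passes 5% of the time, which is alpha.

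**4. Smaller midwife effect, VI equal to control, proper 13-point test, unclustered.**

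| True MW effect | Control 27% | Control 61% |
|---|---|---|
| 5 points | 66% | 61% |
| 8 points | 35% | 34% |
| 10 points | 19% | 18% |
| 13 points | 5% | 5% |

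Example, 5 points and control 27%: SE = √(0.32 × 0.68/271 + 0.27 × 0.73/271) = 0.0391, and Φ(0.08/0.0391 − 1.645) = 66%.

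**5. If the limit is a fixed rate and control is 61%.** 61 − 32 = 29 points: the floor would lie 29 points below standard care.

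**6. The rule read literally.** Simulation with MW 45%, VI 27% and 80% of each arm per protocol (assumed): the two analyses agree in 99.7% of trials, and in 99.6% of trials both fail the margin. Agreement by itself carries no evidence of non-inferiority.

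**7. Joint power if both sets must exclude −13 points.** Simulation, 45% in both arms, unclustered:

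| Per protocol (assumed) | One-sided 0.05 | One-sided 0.025 |
|---|---|---|
| 80% | about 85% | about 75% |
| 70% | about 80% | about 70% |

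**The case against.** The strongest reply is that the rule should be read with what precedes it. Two sentences earlier the section states the 32% limit, ties it to exclusive breastfeeding at 4 months and names a difference in proportions. The likely intent is that both analyses must meet that limit. This stands as a reading of intent, but the text does not say it, and the sentence that fixes the conclusion contains no limit.

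Several stronger readings are tempting and are not supported:

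- A reader might infer that the stated rule would declare a useless video non-inferior 61–66% of the time. Those figures come from a correct 13-point test with a 5-point midwife effect, not from the agreement rule. On the protocol's own 27% and 45% the figure is 0.2%.
- A reader might infer that the 13-point margin will be applied at 1, 4, 8 and 12 weeks. The limit is derived for the 4-month outcome, and nothing attaches it to the earlier visits.
- A reader might infer from Planned Data Analysis that MW versus VI will be judged by a difference test alone. That section condenses the analysis and does not label the comparison so. Its silence does not repair the rule, but it is not a second error.

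It is also fair to say that the protocol gave a reason for its margin and that VI against control is already sized. However, the primary comparison pools the arms, so a pooled benefit could come from MW alone, and nothing makes the VI-versus-control result a condition of the claim.

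**Conclusion.** The point holds as a defect in a stated rule. Agreement between the intention-to-treat and per-protocol analyses is not a test of non-inferiority, and the article ties the conclusion to no margin.

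The limit is also ambiguous between a rate and a difference, and its protection is conditional. It is sound at 27% and 45%. It weakens once the true midwife effect is below 13 points, because a video with no benefit then lies inside a 13-point margin. The size depends on that unknown effect: 61–66% at 5 points, 34–35% at 8 and 18–19% at 10, for 271 per arm, one-sided 0.05, no clustering, and control at 61% or 27%. Since the midwife effect is something the trial sets out to learn, the claim should not rest on assuming it.

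This is not evidence that the sponsor intends to call two failed analyses a success.

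**What to change.** Replace the agreement sentence with a criterion: VI is non-inferior to MW only if the lower one-sided 95% confidence limit for the risk difference VI minus MW in exclusive breastfeeding at 4 months is above −13 points in both the intention-to-treat and the per-protocol sets. This keeps the protocol's one-sided alpha of 0.05. Define the margin as a difference and drop the 32% rate. Add that the video may be said to replace the midwife session only if VI alone is also superior to control, a comparison that Sample Size already covers.

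Cost: the text change is small, but the claim becomes somewhat harder to reach. Joint power for the two-set test is about 85% if 80% of each arm are per protocol and about 80% if 70% are. These figures assume 45% in both arms and no clustering, and they precede the VI-versus-control condition. Any design effect would lower them, although allocation to MW or VI is individual within site, so the full inflation in step 1 is probably cautious. The stated 80% should be rechecked for the joint rule. Moving to one-sided 0.025 as well would take joint power to about 75% or 70%, below the stated figure, so that change is not recommended as part of this correction.
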